### **2.2.2 Study Assessments**

#### **2.2.2.1 Study Procedures Recruitment (Reference: Protocol p. 7-8)**

At baseline, a project Research Assistant (RA) will screen the Rheumatology and Endocrinology Clinic rosters (through PowerChart, Hyperspace, and/or Childrens360) to generate a roster of potentially eligible patients with upcoming outpatient appointments, including the Center for Ambulatory Transfusion (CAT-CR). The roster will be given to clinicians or the administrator within the department for approval if requested. The providers will review the list and let the RA(s) know which patients are okay to approach to invite to participate in the study.

The RA(s) will use the clinic roster to contact these eligible patients prior to their clinic appointment. The RA will first send a letter in the mail to participants briefly describing the study. The RA will then call patients closer to their scheduled clinic appointment to provide more details about the study, and to see if interested participants would potentially be able to arrive prior to their clinic appointment or stay after their appointment to complete the study.

If RAs are unable to contact participants prior to their clinic appointment through mail or phone, the RA will approach participants at the time of their appointment to ask about their interest in participating in a research project. The RA will approach participants at the time of their appointment to ask about their interest in participating in a research project. The RA will meet with interested and/or eligible patients in a private space in or near the clinic or the clinic waiting room to explain the purpose and details of the study to interested patients, and answer any questions. For all those who are interested in participation, the RA will ask the adolescent to complete some questions on a tablet computer to verify eligibility.

#### **2.2.2.2 Randomization (Reference: Protocol p. 8)**

For those who are eligible to participate in the study, the RA will then obtain assent and the participant will be randomized into either the intervention or control group. The RA will then administer the recruitment form, measurement battery, and either the test intervention or control intervention based on randomization.

### **2.2.3 Psychoeducation (Reference: Protocol p. 9)**

The psychoeducation intervention includes visually appealing slides on alcohol use for YCMC. The slides contain quotes from research and user-friendly explanations. The intervention is self-administered on a tablet with privacy. Participants can manually advance or choose auto-play, with an average review time of 4 minutes.

Disease-specific versions of the intervention are developed. Each version addresses the health effects of alcohol use on disease processes and treatment for the respective conditions. The intervention aims to evoke emotional resonance and provide factual information about alcohol's risks for YCMC in the social and medical contexts.

### **2.2.4 Assessment Battery (Reference: Protocol p. 9-18)**

#### **Domains**

The baseline assessment battery will be completed before starting the intervention/control. Both intervention and control groups will complete the baseline, 6-month, and 12-month assessments. Our assessment battery will cover:

1. Health information, including medical history.
2. Factors that may influence substance use, such as social support, family structure, extracurricular activities, and mental health.
3. Measures of alcohol, tobacco, marijuana, prescription drug, and other illicit drug use frequency and severity.
4. Intermediate measures related to substance use, such as attitudes, knowledge, risk tolerance, availability, and future use. Measures related to the participant's personality, such as self-efficacy and grit, will also be included.
5. Disease-specific questions about the burden of disease and disease management.

We will use previously validated tools selected for their clinical and research utility, simplicity, ease of administration, and interpretation. Participants will enter their questionnaire responses into a tablet computer at baseline. Follow-up assessments at 6 months and 12 months will be conducted over the phone or in person by the RA.

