For re-administration of the adolescent assessment battery, an e-mail will be sent to all participants with a link to a 6 month follow up survey and another e-mail with a link to a 12 month follow up survey. In order to maximize follow up rates, the recruitment window for Research Assistants to contact patients will be 5-8 months post baseline for the 6 month follow up battery and 11-14 months post baseline for the 12 month follow up battery. An e-mail will be sent to participants with a link to the follow up survey. E-mail reminders will also be sent to those that receive the survey through e-mail but do not complete them. If for some reason completing the follow-ups through e-mail is not possible or participants do not complete them after receiving the reminders, the survey can be administered over the phone by one of the research staff.

At the 6-month and 12-month follow up, each participant will be sent an email that reminds them about the study, and explains the purpose and details of the follow up assessment. Each email will contain a link to the follow-up survey that is attached to the individual participant's study ID number and administered through REDCap. Surveys sent to participants will follow all privacy and confidentiality guidelines as set through REDCap and BCH. Participants will receive two reminder emails to complete the follow-up assessment surveys online. If a participant has not completed the follow-up assessments after two reminders, the RA will attempt to contact the participant by phone and/or text to remind them about the follow up and request completion, or to administer the follow-up assessment by phone if the participant is unable to complete the battery online. Before administering the assessment battery by phone, the RA will ask the participant to verify that he/she is in a private setting where their answers cannot be overheard by others.

Participants who have turned 18 by the time of follow up will be re-consented over the phone prior to completing the follow up surveys through e-mail. The RA will administer the consent form over the phone and obtain verbal consent in lieu of the written assent form administered at baseline

Upon completion of the survey online, the RA will receive a notification from REDCap that the survey has been completed, and will send the participant remuneration, either in the form of electronic gift card via email, or physical gift card via mail, depending on participant preference.

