407 confusion. The RAs will record participant responses and compare notes following the interview. The  
408 assessment battery and intervention will be adapted as needed based on participant comments.

409 **Assessment Battery:** The baseline assessment battery will be completed before administering the  
410 intervention/control. Participants in both the intervention and control arms will complete the baseline, 6  
411 month, and 12 month assessment batteries. Our assessment battery will consist of 1) health  
412 information including medical history 2) factors that may affect substance use such as social support,  
413 family structure, extracurricular activities, and mental health 3) measures for alcohol, tobacco,  
414 marijuana, prescription drug, and other illicit drug use frequency and severity; which will include  
415 questions about the participant’s own use and friend’s use 4) intermediary measures related to  
416 substance use such as perceived attitudes, knowledge, fears, availability, and future use will be  
417 included as well as measures related to the participant’s personality such as self-efficacy and grit 5)  
418 disease specific questions related to burden of disease and disease management. When possible, we  
419 will use previously validated tools selected for high clinical and research utility, parsimony, ease of  
420 administration and interpretations. At baseline, questionnaire responses will be entered into the tablet  
421 computer by the participant. During the 6 month and 12 month follow up, assessment batteries will be  
422 administered over the phone or in person by the RA.

423 The assessment battery consists of questions from previously validated surveys, as well as novel  
424 questions that were created for this study. The goal was to develop an assessment battery that was  
425 easy to administer, brief, and had good predictive validity for youth. In instances where we wished to  
426 calculate the total score for each participant such as the 8-Item Grit Scale and the Patient Health  
427 Questionnaire-2 (PHQ-2), the entire questionnaire was included. For measures where we were  
428 interested in a more specific outcome such as grades in school or injuries related to alcohol, we  
429 selected questions from larger scales such as the Monitoring the Future study or the Personal  

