**Disease Knowledge:** A previous study by the Co-PIs also showed that knowledge about whether alcohol can interfere with medications or laboratory tests used to treat chronic conditions was low among YCMC. Alcohol use among youth with type 1 diabetes can pose serious health risks such as hypoglycemia. A common theme in the qualitative work by the Co-PIs was a preference from adolescents for direct and honest information about the disease-specific risks of substance use without “any gray areas” or “sugarcoating” information. The knowledge section will focus on presenting information about how alcohol is processed in the body and how this may impact chronic conditions or the effectiveness of the medications used to treat chronic conditions.

**Control:** Those in the control arm will receive information/brief advice around internet safety. Information for the internet safety was adapted from existing curriculum available through Netsmartz and KidsHealth.org. The core topic around internet safety will focus on how youth can protect their online presence and increase awareness of their “digital footprint”. We will provide information on the importance of being safe about posting online, possible consequences of what posting personal information, and protecting online privacy.

**Follow-up Assessment:** We will follow up with the recruited sample 6 months and 12 months post baseline. We will administer an abbreviated Assessment Battery, either online or via phone, with a focus on changes in behavior since baseline to measure substance use and outcome trajectories over time. The assessment batteries administered at 6 and twelve months post baseline are attached to this protocol.

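### The documents conflict on whether the 6- and 12-month follow-ups are research-assistant interviews or online self-report, and nothing masks the callers to arm

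*Supplement*

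**What the plan says.** The two documents describe follow-up in three ways.

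- **RA by phone or in person.** SAP 2.2.4: "Follow-up assessments at 6 months and 12 months will be conducted over the phone or in person by the RA". The Assessment Battery paragraph of protocol section D matches it: "During the 6 month and 12 month follow up, assessment batteries will be" "administered over the phone or in person by the RA". Neither mentions an online route.
- **Online for all, phone as fallback.** Protocol section D, Recruitment: "an e-mail will be sent to all participants with a link to a 6 month follow up survey", with a second link at 12 months, both through REDCap. Then: "If a participant has not completed the follow-up assessments after two reminders, the RA will attempt to contact the participant by phone and/or text". Phone administration is open to any staff member: if "participants do not complete them after receiving the reminders, the survey can be administered over the phone by one of the research staff".
- **Online or phone, with no order of preference.** The Follow-up Assessment paragraphs of the protocol and of SAP 2.2.5: "We will administer an abbreviated Assessment Battery, either online or via phone". Neither mentions an in-person route.

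Baseline is self-entry: "Participants will enter their questionnaire responses into a tablet computer at baseline". SAP 2.2.2.2 has the RA administer the test or control material according to randomisation. The SAP 11.0 update of 6/27/2019 makes past 3-month alcohol use, from a brief frequency item, the primary outcome. The update of 12/16/2020 models it from baseline to twelve months. No SAP update and no entry in the amendment summary settles the follow-up mode.

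**The concern.** The primary outcome is an adolescent's own report of drinking, so how and to whom it is reported matters. One arm has seen material on alcohol risk and the other on internet safety. A live interviewer who knows the arm could probe or record differently. A respondent who connects the caller with the alcohol material could disclose less. If either happens more in the intervention arm, reported drinking falls there without any change in behaviour, and the trial shows a benefit that is not real.

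Which passage governs decides how many participants are exposed to this: all of them under SAP 2.2.4, only reminder non-responders under Recruitment. The phone share could also differ by arm, and neither document says that mode is recorded, so the analysis might not be able to show it.

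**Working it through.** The plan states no figure on this point, so the check compares passages and then gives an illustration of scale.

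**1. Is the conflict in current text?** Yes, and inside each document. SAP 2.2.4 (phone or in person) disagrees with SAP 2.2.5 (online or phone). The protocol's Assessment Battery paragraph disagrees with its Recruitment and Follow-up Assessment text.

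**2. Does the follow-up caller know the arm?** The RA role gives out the arm-specific material and therefore knows the allocation. No passage masks RAs, restricts their view of allocation, or assigns separate follow-up staff.

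**3. Is the mode the same as at baseline?** Not under SAP 2.2.4: tablet self-entry first, live interview later. The Timeline Follow Back is likewise described only as a self-administered electronic calendar, with no interview form.

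**4. Scale if disclosure differs by arm.** Assumptions, none from the documents: true past 3-month use 30% in both arms; disclosure 90% in the control arm; disclosure 5 or 10 points lower in the intervention arm when interviewed; a fallback phone share of 30%.

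Observed use = 0.30 × disclosure; odds = p/(1 − p); OR = intervention odds / control odds.

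- Control: 0.30 × 0.90 = 0.270; odds 0.270/0.730 = 0.370.
- All interviewed, 5 points lower: 0.30 × 0.85 = 0.255; odds 0.255/0.745 = 0.342; OR 0.93.
- All interviewed, 10 points lower: 0.30 × 0.80 = 0.240; odds 0.240/0.760 = 0.316; OR 0.85.
- 30% interviewed, average gap 1.5 points: 0.30 × 0.885 = 0.2655; odds 0.2655/0.7345 = 0.361; OR 0.98.
- 30% interviewed, average gap 3 points: 0.30 × 0.87 = 0.261; odds 0.261/0.739 = 0.353; OR 0.95.

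**5. Effect on the false-positive rate.** Inputs: 150 per arm (the 300 expected completers in SAP 9.0, assuming equal allocation); two-sided 0.05; no true effect; prevalence 0.308 (the past-year alcohol figure in protocol section C, as a stand-in); under-reporting in the intervention arm only, and only when interviewed. Here the OR is control versus intervention, the direction used in SAP 9.0. The nominal chance of a significant result favouring the intervention is 2.5%.

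| Relative under-reporting | All interviewed: OR, chance | 30% interviewed: OR, chance |
|---|---|---|
| 5% | 1.076, 4.8% | 1.022, 3.1% |
| 10% | 1.161, 8.5% | 1.045, 3.7% |
| 20% | 1.361, 22.1% | 1.092, 5.4% |

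**6. Under-reporting equal in both arms.** With a true OR of 2.0, intervention prevalence 0.308 and 90% of users disclosing in each arm, the observed OR is 1.92 and power is 0.76 instead of 0.83. A shared mode shift therefore dilutes the effect and does not create one.

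**The case against.** Recruitment is the only passage with a working procedure: link, two reminders, then phone. SAP 2.2.4 cites the protocol pages and repeats the battery paragraph, so it may be an inherited summary line and not a decision to interview everyone. That is a fair reading, but the text as written directs otherwise and no update corrects it.

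The disclosure gap is an assumption, applied only in the favourable direction. Under the Recruitment procedure with the assumed 30% share it moves the OR to no further than about 0.95, small beside the design OR of 2.0. Participants know what they viewed, so arm-related reticence could also occur online, and masking callers would not remove it. Phone calls carry a safeguard: the RA asks the participant to confirm a private setting. These points stand, and they limit the size of the concern.

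A reader might go further and infer that the person who randomised and treated a participant later interviews that same participant. The documents do not support this. Assignments are randomly generated within strata (SAP 11.0, update of 11/15/2016), the intervention is self-administered on a tablet (SAP 2.2.3), and the RA is named as a role. The same person calling back is possible but not stated.

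**Conclusion.** The conflict is real, stands in current text and bears on how the primary outcome is collected. Follow-up callers come from staff who may know the arm, and nothing masks them. That is enough to require a correction.

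It does not show that the result is biased. Bias needs disclosure, or the mix of modes, to differ by arm, and the documents hold no evidence on either. Nor does the change from tablet to interview by itself bias the comparison: if it acts equally in both arms it mainly weakens a true effect. The illustrative range is an OR of about 0.93 to 0.85 if all are interviewed and about 0.98 to 0.95 if about 30% are. It rests wholly on the assumed 30% prevalence, 90% control disclosure and 5 to 10 point gap.

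**What to change.** 1. Replace the follow-up sentence in SAP 2.2.4 and in the protocol's Assessment Battery paragraph with the Recruitment procedure: a self-administered REDCap link, with phone only after two reminders. Align the Follow-up Assessment paragraphs of both documents.
2. Have fallback calls made by an existing RA who did not enrol that participant and whose REDCap rights hide the arm.
3. Record the mode of every assessment and report it by arm at 6 and 12 months.
4. Keep the intention-to-treat analysis of all responses primary. An analysis restricted to self-administered responses is supportive only, because mode arises after randomisation and may differ by arm, so the restriction can itself introduce selection.

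The cost is text edits, one user-rights setting, one extra variable, one extra table, and a small constraint on which RA calls whom. The last SAP update is dated 09/28/2023 and is labelled post hoc, so follow-up may already be complete. In that case, correct the text to what was done, state whether callers knew the arm, and report mode by arm where it was recorded.

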### **2.2.5 Measures (Reference: Protocol p. 9-18)**

**Health information:** Past medical history may inform a participant's decisions to use or abstain from alcohol and other drug use. Youth may use illicit substances to self-medicate, or may avoid substances because of specific health concerns. We will ask participants to report past medical history, and to rate their overall health. We will use previously validated questions to assess these domains. A question on past medical history about being treated with prescribed medications for anxiety, depression, or ADHD was created novel for this battery.

**Other factors that may affect substance use:** Multiple components of the day to day life of youth may predict a relationship to substance use patterns. Predictors of interest for this project include social support, parental monitoring and communication, sleep, and family medical history.

**Current mental health status:** The PHQ-2 is a self-administered, 2-item scale for detecting depression using DSM-IV diagnostic criteria. The PHQ-2 has been studied extensively in large populations and

comes with considerable evidence for its validity. The PHQ-2 has been used extensively in primary care settings and adolescent populations. We will be administering the full PHQ-2 at baseline, 6 month follow up, and 12 month follow up.

The GAD-2 is a self-administered, 2 item scale to screen for anxiety disorders. It has high sensitivity and specificity for detecting generalized anxiety disorder and has been used in primary care settings. We will be administering the full GAD-2 at baseline, 6 month follow up, and 12 month follow up.

**Alcohol, tobacco, marijuana, and use of other substances:** We will administer a series of questions about frequency of substance use and validate them against the criterion standard TLFB.

**Substance use screen:** We will administer the Screening to Brief Intervention (S2BI) to ask about alcohol, tobacco, marijuana, prescription drug, and other substance use over the past 12 months. S2BI was developed at BCH with support from NIDA. In the original S2BI, questions on prescription drug use are asked only if patients answer yes to using alcohol, marijuana, or tobacco. In this study we will ask all participants about prescription drug use regardless of their use of other substances. Following the format of the S2BI, questions about other psychoactive substances including illegal drugs (such as cocaine or Ecstasy), inhalants (such as nitrous oxide), and herbs and synthetic drugs (such as salvia, “K2” or bath salts) will be asked only if participants answer yes to either alcohol, marijuana, or tobacco use.

**Criterion standard for substance use disorder diagnosis:** If participants answer no to past 12 month alcohol, marijuana, or tobacco use they will be asked a question about lifetime use of these substances. Questions about lifetime use were taken from the Computerized Diagnostic Interview Schedule for Children – 4 (DISC-IV).

**Alcohol safety screen:** We will include questions about frequency and severity of alcohol use that will be used as safety flags. If a patient reports consuming 10 or more drinks containing alcohol in the past three months, or using sedatives in combination with alcohol, the RA will notify the primary clinician (See Adverse Event Criteria and Reporting Procedures)

**Prescription medication misuse:** Abuse of prescription medications among youth has risen dramatically in recent years. We will ask questions to assess if participants take medication as prescribed by their doctor. We will also assess medication diversion, with a specific interest in patients who are being prescribed stimulant medications. These questions were adapted from previous studies on prescription medication misuse among adolescents.

**Criterion standard substance use frequency measure:** Each participant who reports any alcohol use will complete a 90-day Timeline Follow Back (TLFB) calendar that records frequency and quantity of alcohol use and frequency of marijuana use. The 90-day TLFB has been demonstrated to be both valid and reliable in adolescents. Participants will complete the TLFB on the computerized tablet following completion of the assessment battery. The TLFB is self-administered; participants will view an electronic calendar of the past 90 days and will input if they used marijuana on a given day and/or number of drinks consumed on a given day. If participants have not used marijuana or consumed a drink in the past 90 days, they will click through the calendar leaving the days blank. On the last screen they will be prompted to confirm that they did not select any days. The tool will be programmed to calculate total days of use and number of drinks.

**Intermediary measures:** We hypothesize that the following questions may serve as intermediary measures to predict long term substance use outcomes.

**Time spent with alternative activities:** Studies have shown that involvement in school based extra-curricular activities is generally related to less substance use among adolescents except in the case of athletic participation which has shown a positive relationship to substance use. We are interested in the number of hours participants spend per week engaged in different activities.

**Academic and extracurricular performance:** Engagement, performance, and interest in academics and extracurricular activities, as well as disciplinary consequences may be indicators of current or future substance use. We will ask participants about personal consequences related to substance use. We are interested in consequences related to school such as academic performance, their commitment to school and extra-curricular activities, and how often they receive detention.

**Perception of overscheduling:** We will ask questions based on whether or not adolescents view themselves as overscheduled taken from the Measure of Perceived Over-Scheduling (MOPS) scale. We selected three items from the MOPS scale one from each factor measurement: pressure from external forces to participate in activities, feeling overwhelmed by participation, and preference for one's activities.

**Acceptability and interest in app/tools to monitor health behaviors/ Internet and social media use:** We will ask questions about participant's willingness to use cellphone apps and tools to monitor health behaviors. This may provide information that can be used to inform development of health behavior interventions. Other factors that may also be of interest in informing interventions are the presence of alcohol and other drugs on social media websites and participant's use of the internet to search for information about alcohol or other drugs. These questions were created novel for this study.

**Possible reasons to abstain from alcohol and marijuana use:** We are interested in learning more about different reasons participants may choose to abstain from alcohol and marijuana use. We will ask participants to rate the importance of different statements as reasons to abstain from alcohol and marijuana. We will also assess whether perceived parental attitudes about smoking marijuana has an impact on marijuana use.

**Knowledge about the impact of marijuana and alcohol on health:** Brief interventions to prevent or reduce adolescent substance use often focuses on increasing youth knowledge of the harms associated with use, with the expectation that increased knowledge will lead to decreased use over time. We will ask novel questions to assess participants' knowledge on the effects of substance use.

**Perceived risk of harm from substance use:** In nationally representative surveys, perceived risk of harm related to substance use is strongly associated with marijuana use on a population level, though less is known about the predictive validity on an individual level. We will ask participants questions regarding perceived risk of harm of alcohol, marijuana, tobacco and prescription medications in order to describe associations between perceived risk of harm and substance use trajectories.

**Perceived availability of alcohol and marijuana:** Increased availability of alcohol has been associated with increased alcohol use and related problems in youth. To look at perceived availability of substances and the correlation with substance use on an individual level, we will ask a question about how difficult it would be for participants to get alcohol and marijuana if they wanted some. These questions were taken from the Monitoring the Future study.

**Perceived likelihood of future substance use:** We will use questions from Monitoring the Future that ask about likelihood of future use validated in a longitudinal sample to determine whether this question is a good proxy measure of future use. We will ask participant about their likelihood of substance use three

months from when they are completing the assessment battery and analyze responses against reports of actual substance use collected longitudinally.

**Receipt of healthcare advice about substances from a medical professional:** To determine adolescents' experience of physician screening we will whether a clinician has asked about substance use and willingness to talk to a clinician or learn more about how alcohol use can affect health. We will use questions that were piloted by the research team in a previous project (NIAAA number).

**Confidence in refusal skills:** We are interested in learning about participant's confidence in their ability to refuse substances from friends. An adolescent's peers can have an influence on their behavior or substance use. We will include one novel question in our battery to assess participant's perceived self-efficacy.

**Grit:** Perseverance and passion for long term goals may predict substance use trajectories. We will be administering the 8-Item Grit Scale, which is a two factor model that measures consistency of interest and perseverance of effort. The Grit Scale has been used in research settings and has been validated in both adult and adolescent populations. In these populations it has been used to look at relationships in educational attainment, career changes, and predicted GPA. We will include all 8 items from the Short Grit Scale in our assessment battery.

**Future goals for after high school:** Goals for the future may predict substance use by high school students. This has been studied in adjudicated adolescents, where positive future orientation was associated with lower levels of substance use. There has been little research in goal setting and future orientation as a predictor for other populations of adolescents. We would like to include a section on future goals in our assessment battery to study it further as a predictor for substance use. We will ask participants whether they have plans for their future after high school.

